### Power calculations

On the basis of the Moving Sound pilot study, it is assumed that the mean sedentary (i.e., sitting or lying down) time will be 7 h 40 min per day at baseline. It is also assumed that the reduction in sedentary time in the intervention group at the end of the study will be around 6 % while the control group’s figure remains unchanged. Differences of groupwise means are tested via T-tests. Power calculations for the study (see Table 1) show that if the significance level is 0.05 (α = 0.05) and the power of the study is to be 80 % (β = 0.80), effect size varies from 0.357 to 0.500 and approximately 63–124 mother-child pairs per group are needed.

**Table 1 Tab1:** Power calculations for the primary outcome of the study

Primary aim: decrease participants’ sedentariness by using movement-to-music video material							
Sedentary time (mean 7 h 40 min, α = 0.05)			Intervention: Accelerometer and DVD group		Control: Accelerometer group		Number of participants (mother + child pair) needed per group
Reduction of sedentary time	power	effect size	Mean	SD	Mean	SD	
5.4 %	β = 0.80	0.357	435 min	70 min	460 min	70 min	124
5.4 %	β = 0.80	0.385	435 min	65 min	460 min	65 min	107
5.4 %	β = 0.80	0.417	435 min	60 min	460 min	60 min	91
6.5 %	β = 0.80	0.429	430 min	70 min	460 min	70 min	86
6.5 %	β = 0.80	0.462	430 min	65 min	460 min	65 min	74
6.5 %	β = 0.80	0.500	430 min	60 min	460 min	60 min	63

α = significance level, β = power of the test

### The interventions

The mothers and children will wear the accelerometer on an elastic belt on their hips for the first 14 days (two weeks) and last seven days (during week 8; see Fig. 2). Both groups will complete an exercise diary during weeks 1, 2, and 8. The intervention group will fill in questionnaires at baseline and after two and eight weeks, with the control group doing so at baseline and after the full eight weeks.

**Fig. 2 Fig2:**
[figure not shown]
Intervention for eight weeks

In addition, the intervention (i.e., movement-to-music) group will receive the DVD and YouTube-link to videos by e-mail or cell phone, in line with their choice between these, at the end of the first week. The DVD is the preferred option, because of the larger image and better sound when it is played through a television set. The YouTube-link is intended as an alternative to be used, for example, during trips or if the DVD breaks. Mothers in the movement-to-music group will be instructed to watch the program on the DVD or on the Internet every other day with their 4–7-year-old child. The mothers and children will be instructed to move to the video and report their exercise in the structured diaries. Mothers will also use the Brunel Music Rating Inventory-2 (BMRI-2) to assess the motivational quality of the music used in the movement-to-music video [28, 29].

## Outcome measurements and pre-testing

### Outcomes

**The main objective** of the study is to decrease SB and increase PA among the mothers and their children by means of the movement-to-music video program.

**The primary outcomes** of the study are SB and PA, which will be assessed objectively by means of the accelerometer and further examined via the exercise diaries and questionnaires. Measurements will be performed in the first, second and eighth weeks of the intervention. For inclusion in the analysis, accelerometer data for at least four days per week and measurement time of more than 10 h per day will be needed. Participants using the accelerometer on fewer than four days per week will be excluded. Any participants whose measurement time for a given day is over 20 h will be considered to have slept with the accelerometer. To avoid possible bias in SB time, the recording time for them will be capped at 20 h, with the deduction coming from their lying-down time. The measurement discriminates among the time spent in a sitting or reclining posture, standing still, and PA. The daily amount of standing-up (breaks in sedentary time) will be calculated from the number of lying/sitting periods that end with standing. Lying, sitting, and standing time, along with light, moderate, and vigorous PA time during waking hours, will be analyzed both in minutes and as a proportion of the measurement time (at least 10 h per day). In the analysis, moderate and vigorous activity might be combined as MVPA if vigorous PA covers a very small proportion of the total measurement time.

**Secondary outcomes** of the study include the quantity of self-reported sitting and screen time among mothers and children, motivation to exercise, and the motivational quality of the music and movement-to-music video. Additional secondary outcomes are mother’s weight and quality of life, depression, anxiety, perceived health, and work ability assessed by a questionnaire.

**The specific aim** is to study the effectiveness of the intervention by comparing accelerometer use alone with a combination of accelerometer and movement-to-music video program for mother-child pairs.

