**Methods:**

Mother-child pairs (child age of 4–7 years) will be recruited from among NELLI lifestyle-modification study five-year follow-up cohort participants, encompassing 14 municipalities in Pirkanmaa region, Finland.

Accelerometer and exercise diary data are to be collected for intervention and control groups at the first, second and eighth week after the baseline measurements. Background factors, physical activity, screen time, motivation to exercise, and self-reported height and weight, along with quality of life, will be assessed via questionnaires. After the baseline and first week measurements, the participants of the intervention group will receive a movement-to-music video program designed to reduce sedentary time and increase physical activity. Intervention group mother-child pairs will be instructed to exercise every other day while watching the video program over the next seven weeks. Information on experiences of the use of the movement-to-music video program will be collected 8 weeks after baseline. Effects of the intervention will be analyzed in line with the intention-to-treat principle through comparison of the changes in the main outcomes between intervention and control group participants. The study has received ethics approval from the Pirkanmaa Ethics Committee in Human Sciences.

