### Statistical methods

The effects of the intervention will be analyzed in line with the intention-to-treat principle through comparison of the changes in the main outcomes between intervention and control group participants. Level of PA, sedentary time, and body weight will be compared between the intervention and control group. All differences in the afore-mentioned outcomes between groups will be examined via linear regression. If the assumptions of linear regression are violated, ordinal or logistic regression analysis will be used. Non-parametric methods (specifically, the Mann-Whitney *U*-test) will also be used to describe differences between groups if needed. Subgroup analysis within the intervention group will be conducted with the mother’s motivation to exercise with the movement-to-music video program and her musical background as covariates. The intervention group will be split into two classes on the basis of these (dummy) variables. These variables will be used to explain differences in exercise activity between mothers in the intervention group. A significance level of 0.05 will be used for all analysis.

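### The sample size covers one sedentary-time test, but SB and PA are both primary in mothers and children, each tested at 0.05 with no hierarchy or success rule

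*Protocol article*

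**What the plan says.** Three sections of the protocol article describe what is primary, and they do not agree.

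- **Outcomes.** The main objective "of the study is to decrease SB and increase PA among the mothers and their children". The primary outcomes "of the study are SB and PA, which will be assessed objectively by means of the accelerometer". That is two outcomes in two populations, with no ranking. The same paragraph gives the timing ("Measurements will be performed in the first, second and eighth weeks of the intervention") and lists posture and intensity components on two scales. On the PA measure it says that "moderate and vigorous activity might be combined as MVPA if vigorous PA covers a very small proportion of the total measurement time", without a threshold.
- **Power calculations.** Table 1 is headed "Power calculations for the primary outcome of the study", in the singular, and its primary aim is sedentariness alone. The text assumes a mean of 7 h 40 min (460 min) per day, a reduction of around 6 % at the end of the study, t-tests, a significance level of 0.05 and 80 % power. This leads to 63–124 mother-child pairs per group. The section does not say whether the mean and SD belong to mothers or to children, and it gives no power for PA.
- **Statistical methods.** "Level of PA, sedentary time, and body weight will be compared between the intervention and control group", and "A significance level of 0.05 will be used for all analysis". No comparison is singled out as the primary test.

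**The concern.** A reader cannot tell from the article what result would make the trial positive. If any one of the primary comparisons is enough, each tested at 0.05, the overall false-positive rate exceeds 5 %. If the objective is read as requiring an effect in both mothers and children, the error rate between the two is not the problem, but 80 % power for one test is not 80 % power for both. These are alternative readings and their costs do not add up. Under either one, a property that the plan states for a single test does not hold for the conclusion.

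This is not a detail that can be presumed to sit in an unseen analysis plan. The article itself fixes the significance level for all analyses, and it names the primary outcome differently in two places.

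**Working it through.** **1. Reproduce Table 1.** Inputs from the Power calculations section: differences of 25 and 30 min, SDs of 70, 65 and 60 min, α = 0.05, power 80 %, equal groups. Sidedness is not stated. The two-sided normal approximation is

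n per group = 2 × (1.960 + 0.842)² × (SD/difference)² = 15.70 × (SD/difference)²

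| Difference, SD (min) | Calculated | Rounded up | Table 1 |
|---|---|---|---|
| 25, 70 | 123.1 | 124 | 124 |
| 25, 65 | 106.1 | 107 | 107 |
| 25, 60 | 90.4 | 91 | 91 |
| 30, 70 | 85.5 | 86 | 86 |
| 30, 65 | 73.7 | 74 | 74 |
| 30, 60 | 62.8 | 63 | 63 |

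All six figures reproduce. A one-sided test gives about 97 in the first row and does not fit. The arithmetic is correct for one two-sided test at 0.05 of one outcome, and it contains no allowance for a second outcome or a second population.

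**2. Count the documented primary comparisons.** SB and PA, each in mothers and in children: 2 × 2 = 4, at one time point and on one scale.

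**3. Chance of at least one false positive if any of the four suffices.** For independent tests:

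1 − 0.95⁴ = 0.185

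The four tests will be correlated, since SB and PA share the same wear time and the pairs share a household, but the article gives no correlations. Simulating four equally correlated normal test statistics gives:

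| Assumed correlation | At least one of four significant |
|---|---|
| 0 | 18.5 % |
| 0.3 | 17.4 % |
| 0.5 | 15.6 % |
| 0.7 | 13.0 % |
| 0.9 | 9.3 % |

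**4. False claims of benefit only.** A two-sided 0.05 test has a 2.5 % chance of a false result in the favourable direction. For four independent tests:

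1 − 0.975⁴ = 0.096

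At an assumed correlation of 0.5 it is about 7.8 %.

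**5. Joint power if mother and child must both succeed on sedentary time.** Assume 80 % power for each, that is, the same effect and SD in both. If independent, 0.80 × 0.80 = 0.64. From the bivariate normal distribution, 0.67 at correlation 0.3 and 0.69 at 0.5.

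**6. The same with the expected recruitment.** The recruitment section expects 251–335 pairs, about 125–167 per group. Power for one test is approximately Φ[(difference/SD) × √(n/2) − 1.960]. Before any dropout:

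- 25 min, SD 70: 81 % to 90 %. Both, if independent: 0.806² = 65 % to 0.904² = 82 %.
- 30 min, SD 60: 98 % to over 99 %. Both, if independent: 0.977² = 95 % to 0.996² = 99 %.

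**The case against.** The strongest defence is that the article does point to one leading outcome. The Power calculations section gives sedentariness as the primary aim, the accelerometer section calls reducing sedentariness the main aim, and the powered effect is placed at the end of the study. A sympathetic reader could take sedentary time at week 8 as the real primary test. That is a sensible reading and the fix adopts it. It does not remove the conflict, because the Outcomes section still calls SB and PA primary together, and even sedentary time remains two tests, one in mothers and one in children.

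The defence is right on several other points.

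- A reader might infer that week 2, the second scale and every posture and intensity component are primary as well. The video is delivered only after the first week ("After the baseline and first week measurements, the participants of the intervention group will receive a movement-to-music video program"), so weeks 2 and 8 could be counted as two follow-ups. That gives 8 tests (1 − 0.95⁸ = 34 % if independent), and two scales give 16 (1 − 0.95¹⁶ = 56 %). The article does not support this. It says when measurements are taken and how times will be analysed, and it does not call these analyses primary.
- A reader might infer that body weight has been promoted. It has not: mother's weight is listed as secondary, and comparing it between groups does not change that.
- Merging moderate and vigorous activity depends on the share of vigorous activity, not on the group difference, and the Background already ties PA to MVPA minutes. It is a loose end in defining the PA outcome, not evidence of selective choice.
- With strong correlation, or when only false benefit is counted, the inflation is well below the 18.5 % headline.
- The joint-power shortfall shrinks, and under favourable assumptions disappears, if the expected recruitment is reached.

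**Conclusion.** The point stands, limited to four comparisons. The article names one primary outcome where it sizes the trial and two where it defines its outcomes, in two populations, and it fixes 0.05 for all of them with no order or success rule.

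If any one result suffices, the chance of at least one false positive is 18.5 % under independence and about 17 % to 9 % for assumed common correlations of 0.3 to 0.9. For false benefit alone it is about 9.6 % under independence, against 2.5 %. If both mother and child must succeed on sedentary time, joint power at the Table 1 sizes is about 64–69 % for assumed correlations of 0 to 0.5. With 125–167 pairs per group before dropout it ranges, under independence, from 65 % to 99 % across the extreme rows of Table 1.

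The correlations, and equal effects and SDs in mothers and children, are assumptions. The sample-size arithmetic is not at fault; the mismatch lies between what it covers and what is called primary. Nor should a reader take the 460 min and the SDs as mothers' values: Table 1 does not say whose they are.

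**What to change.** Reconcile the Outcomes, Power calculations and Statistical methods sections before any group comparison is seen.

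1. Name one primary test: sedentary time at week 8, on one stated scale, in one stated population. The sponsor should confirm whether the mean and SDs in Table 1 describe mothers or children, so that the named test is the one that was sized.
2. Test the other three comparisons in a fixed order at 0.05 each, continuing only while each is significant: the other population's sedentary time, then PA in each population. The order is the sponsor's choice, since the article does not rank mothers above children.
3. Fix the PA measure now, for example MVPA, instead of leaving the merging of categories until the data are in.
4. Report week 2, the other scale and the posture and intensity components as supportive, with confidence intervals.

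A fixed order keeps the overall error at 5 % and leaves 63–124 pairs per group valid for the first test. Splitting alpha equally over four tests (0.0125 each) would instead need 175 per group in the least favourable row of Table 1, above the expected 125–167, or 90 in the most favourable row.

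The cost is a protocol and registry amendment while recruitment is under way. Outcomes lower in the order can be claimed only if those above them succeed. No extra participants or measurements are needed for the first test; power for those below it, PA in particular, remains unstated.

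### The four-day wear exclusion is not reconciled with the intention-to-treat statement; read literally, the primary comparison is a valid-wear complete-case analysis

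*Protocol article*

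**What the plan says.** All references are to the protocol article.

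- **Outcomes.** The primary outcomes are "SB and PA, which will be assessed objectively by means of the accelerometer". On timing: "Measurements will be performed in the first, second and eighth weeks of the intervention". The entry condition reads "For inclusion in the analysis, accelerometer data for at least four days per week", with more than 10 hours on each day, and the next sentence is "Participants using the accelerometer on fewer than four days per week will be excluded".
- **Statistical methods.** "The effects of the intervention will be analyzed in line with the intention-to-treat principle through comparison of the changes in the main outcomes". The two groups are compared by linear regression. The abstract repeats the principle: "Effects of the intervention will be analyzed in line with the intention-to-treat principle".
- **Recruitment of the study population and randomization.** Mothers are allocated by sealed envelope at the NELLI sampling contact. Data collection says that the accelerometer information is given at that same contact, so all wear follows allocation.
- **The interventions.** The intervention group receives the DVD and link "in line with their choice between these, at the end of the first week". Weeks 2 and 8 therefore also follow the start of treatment.

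The article does not say whether one failed week removes the person or only that week, whether a failure by mother or child removes the pair, or how the resulting missing outcomes are handled.

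**The concern.** Intention-to-treat compares everyone randomised, in the arm to which they were assigned. A rule that removes people because of something they did after randomisation breaks that comparison, unless exclusion is unrelated to outcome or acts identically in both arms.

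There are reasons to think that wear could differ by arm. Participants know whether they received the video. The intervention group also has an extra questionnaire at week 2 and is asked to exercise every other day. If those who stop wearing the belt also change less, and do so more often in one arm, the analysed difference is partly selection.

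The planned comparison of changes adds to this. A change needs a valid week 1 and a valid later week, so ordinary regression on change scores drops anyone who lacks either, even if the wear rule is read as applying to single weeks.

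**Working it through.** **1. The plan's own sample size.** Inputs from Power calculations, Table 1: difference 25 or 30 min, SD 70, 65 or 60 min, alpha 0.05 (taken as two-sided), power 0.80.

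n per group = 2 × (1.96 + 0.842)² × (SD/difference)² ≈ 15.70 × (SD/difference)²

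| Difference | SD 70 | SD 65 | SD 60 |
|---|---|---|---|
| 25 min | 123.1 → 124 | 106.1 → 107 | 90.4 → 91 |
| 30 min | 85.5 → 86 | 73.7 → 74 | 62.8 → 63 |

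All six table entries reproduce. They contain no allowance for wear exclusion.

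**2. Share with a usable change.** The documents give no wear rate, so this is an assumption. Let each week be valid with probability p, independently. A change from week 1 to week 8 needs two valid weeks:
- p = 0.85: 0.85² = 0.72
- p = 0.95: 0.95² = 0.90

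People who fail one week are likely to fail another. Such correlation raises the share with both weeks valid, to p itself at most.

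**3. What remains per arm.** The expected recruitment is 251 to 335 pairs, or about 125 to 167 per arm. At an assumed 20 % exclusion:
- Low end: 0.8 × 125 = 100. This covers the requirements of 91, 86, 74 and 63, but not 107 or 124.
- High end: 0.8 × 167 = 133.6 ≈ 134. This covers all six.

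For the most demanding row (25 min, SD 70), power = Φ(25 / (70 × √(2/n)) − 1.96):
- n = 100: Φ(2.53 − 1.96) = 71 %
- n = 133.6: Φ(2.92 − 1.96) = 83 %

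**4. Possible selection bias when the treatment does nothing.** Suppose the mean change over all randomised is 0 in both arms, and excluded participants' change is less favourable than that of the included by s min/day. If a fraction e is excluded, the included have mean change −s × e. The analysed difference is then −s × (e in intervention − e in control). Type I error is evaluated at 124 analysed per arm with SD 70 (standard error 70 × √(2/124) = 8.89 min). All rates and shifts are assumptions.

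| Excluded, intervention / control | s | Spurious difference | Type I error |
|---|---|---|---|
| 10 % / 10 % | 30 or 60 | 0 | 5 % |
| 20 % / 10 % | 0 | 0 | 5 % |
| 20 % / 10 % | 30 | −3 min | 6.3 % |
| 20 % / 10 % | 60 | −6 min | 10.4 % |
| 30 % / 10 % | 30 | −6 min | 10.4 % |
| 30 % / 10 % | 60 | −12 min | 27.1 % |

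The planned effect is 25 to 30 min. The first two rows show the conditions under which nothing goes wrong. If the control arm were the one with more exclusions, the sign would reverse.

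**The case against.** The best defence is that a minimum-wear threshold is a data-validity rule. Both arms wear the belt, wear is how the outcome is measured, and a week with too little recording does not measure sedentary time. The problem is then ordinary missing outcome data, and a journal article commonly leaves its handling to the full protocol or analysis plan.

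Much of this stands. The threshold is reasonable for a week's measurement, and the absence of a missing-data section would be no finding. What remains is that the article makes two explicit statements about who enters the primary comparison, and they do not agree.

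Several stronger readings are tempting but not supported:
- **One bad week discards the person.** This is the literal reading of the exclusion sentence, but the condition is framed per week and may concern only that week's data. The text does not settle it.
- **All three weeks, or both members of the pair, must be valid.** Neither is written. Much lower retention figures can be produced by assuming them.
- **The analysed set is per-protocol or made up of compliant users.** The rule does not select on video use. A mother who never plays the DVD but wears the belt stays in.
- **The effect is inflated.** That requires the excluded to be mainly intervention pairs who did poorly. Nothing in the article establishes this.
- **The sample will be too small.** Step 3 shows that this depends on recruitment and on which Table 1 row applies.

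**Conclusion.** The conflict between the exclusion rule and the intention-to-treat statement is explicit and concerns the primary outcomes. As written, the comparison of changes is a valid-wear complete-case analysis carrying an intention-to-treat label. It can be biased, but only if non-wear is related to both arm and outcome.

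Size and direction cannot be derived from the documents. Under assumed exclusion of 20 to 30 % against 10 % and a shift of 30 to 60 min, selection alone would give 3 to 12 min. With exclusion unrelated to outcome, or acting identically in both arms, it gives none. Loss of precision is likewise conditional: at 20 % exclusion, the low end of recruitment misses the two largest Table 1 requirements and the high end misses none. The Table 1 arithmetic itself is correct.

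**What to change.** - Keep the four-day, 10-hour criterion, but state that it decides whether a measurement week is valid. Apply it to mother and child separately, so that neither a failed week nor the other member's failure removes a person.
- Analyse all randomised participants with at least one valid week, in their assigned arm, with a mixed model for repeated measures (weeks 1, 2 and 8, group by week). Make the week-8 contrast the main comparison. Because week 1 follows randomisation, say whether that contrast is in level or in change from week 1.
- Report the number of invalid weeks and of people without usable data, by arm.
- Add a sensitivity analysis in which week-8 data are missing not at random, and include those with no valid week, whom the mixed model leaves out. Self-reported sitting time, scheduled for both groups at baseline and week 8 (Table 3), can inform the imputation.
- Keep the valid-wear completer analysis as a secondary analysis and call it complete-case.

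The cost is a wording change in Outcomes and Statistical methods and slightly more analysis work, with no new data. The main model would rest on a missing-at-random assumption, which is why the sensitivity analysis is needed.

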## Background

The risk of many chronic diseases, among them type 2 diabetes, obesity, breast cancer, and cardiovascular diseases, along with all causes of mortality, grows in consequence of increasing of sedentary behavior (SB) and decreasing of physical activity (PA) [1, 2]. For our research, we have slightly adapted the definitions from the Sedentary Behavior Research Network [3] and Tremblay et al. [4] thus:Sedentary behavior is any waking behavior characterized by energy expenditure ≤1.5 METs while the participant is in a sitting or reclining posture. Screen time (watching television, using a computer, and playing video games or using other screens) is included in SB.Physical activity consists of meeting the established guidelines for physical activity [5], usually reflected in achievement of at least a certain threshold (see below) number of minutes of moderate to vigorous physical activity (MVPA) per day.Physical inactivity consist of performing insufficient amounts of MVPA – i.e., not following the specified physical activity guidelines.

The Centers for Disease Control and Prevention (CDC) recommends that adults engage in at least 150 min of moderate or 75 min of vigorous intensity activity, or an equivalent combination of aerobic activities every week in bouts of 10 or more minutes. In addition, muscle-strengthening activities for all major muscle groups on two or more days per week are recommended [5]. For children, the recommendation includes at least 60 min of aerobic activity per day and muscle and bone strengthening three or more days a week [5]. In addition, there are guidelines for both adults and children to reduce SB by minimizing their sitting, screen time, and motorized transportation [6–10].

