## Methods

### Design and ethics issues

A randomized controlled trial (RCT) is being used, with a parallel design involving one intervention and one control group of mother-child pairs. Mothers and children in the intervention group will receive a movement-to-music DVD and be instructed to exercise with it every other day. The target is to reduce SB and increase PA, in other words, sit less and be more active.

In the study, SB and PA are objectively assessed by means of an accelerometer in the first, second and eighth week of the intervention period. The accelerometers are attached to a flexible belt, which all women and children will be instructed to wear around their hips. The instructions specify using the accelerometers for 14 consecutive days (two weeks) during the participants’ waking hours at the beginning of the study and for seven days (one week) over the last week of the intervention. The accelerometers are to be removed before the participants go to bed and for showers, bathing, swimming, and other water activities. Measurements from accelerometers have been used in earlier studies for both adults and children, and they have been found to be a safe and reliable way to show changes in SB and PA [21]. There are no physical risks with the measurements in this study.

The information on the mothers’ background, motivation, and current health behavior comes from questionnaire data. The questionnaires are identical to those used in the Lifestyle, counseling, and exercise in maternity care (NELLI) five-year follow-up project.

Use of the movement-to-music video program as instructed (10–30 min every other day) will amount to less than half of adults’ and about 10–15 % of children’s PA guideline totals. The reason for this is to reduce risk of musculoskeletal injury and other complications. Moreover, when the movement-to-music video program is used in line with the instruction, there is no significant overall physical overload risk either. It is also assumed that adherence to the video protocol will be better with a short bouts of exercise compared to longer, although the evidence is contradictory [22].

Participation in the research is completely voluntary. Recruited mothers will give written informed consent for participation in the study on their and their child’s behalf. The persons recruited have the right to refuse to participate or to withdraw at any time from the study without explaining the reason.

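### The 20 h cap leaves recorded sleep in sedentary time on days when the accelerometer was worn overnight, contrary to the waking-only definition of the primary outcome

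*Protocol article*

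**What the plan says.** Four parts of the protocol article bear on this point.

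- Background defines the construct: "Sedentary behavior is any waking behavior characterized by energy expenditure ≤1.5 METs while the participant is in a sitting or reclining posture".
- Design and ethics issues gives the wear instruction: "The accelerometers are to be removed before the participants go to bed".
- Power calculations counts posture, not wakefulness: "the mean sedentary (i.e., sitting or lying down) time will be 7 h 40 min per day at baseline". Table 1 then plans on group means of 435 or 430 min against 460 min.
- Outcomes sets the rule for long recordings: "Any participants whose measurement time for a given day is over 20 h will be considered to have slept with the accelerometer". The aim is stated as "To avoid possible bias in SB time", and the remedy is that "the recording time for them will be capped at 20 h, with the deduction coming from their lying-down time".

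The same Outcomes paragraph requires at least four days per week with more than 10 h of recording each. It says that the posture and activity times, described as waking-hours times, "will be analyzed both in minutes and as a proportion of the measurement time".

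**The concern.** The rule identifies the right days and then corrects them only in part. Once a day is presumed to include sleep, the waking-only definition requires all of that sleep to leave sedentary time. The cap removes only what exceeds 20 h. The rest remains as lying time, which the power section counts as sedentary.

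A cap at 20 h would remove the sleep in full only for someone awake for 20 h. For anyone else the affected day carries an overstated value of the primary outcome, so the rule misses its own stated aim. The possible cost is extra variance in the primary outcome. If overnight wear shifts between the first and eighth weeks by different amounts in the two arms, the cost is a spurious change.

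**Working it through.** **Planned effect.** Table 1 gives 460 − 435 = 25 min and 460 − 430 = 30 min, with SD 60 to 70 min. The usual two-sample formula for means (two-sided α 0.05, power 80 %, normal approximation) gives 124, 107 and 91 per group for 25 min and 86, 74 and 63 for 30 min. All six match the table, so 25 to 30 min/day is the yardstick.

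**Sleep left after the cap.** Let R be the recorded hours (R > 20), A the waking hours recorded and W the participant's full waking day, so A ≤ W. Assume that sleep is registered as lying.

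- Recorded sleep = R − A.
- Removed by the cap = R − 20.
- Left in sedentary time = (R − A) − (R − 20) = 20 − A, which is at least 20 − W.

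R drops out, so the result does not require 24 h wear. The documents give no W. The range below is an assumption, with the shorter waking days more plausible for a young child.

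| Waking day W (h) | Sleep left on a capped day, 60 × (20 − W) (min) | Added to a 7-day mean by one capped day (min/day) |
|---|---|---|
| 18 | 120 | 17.1 |
| 17 | 180 | 25.7 |
| 16 | 240 | 34.3 |
| 14 | 360 | 51.4 |
| 13 | 420 | 60.0 |

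On the capped day itself, the remainder is 4 (120/30) to 16.8 (420/25) times the planned effect. It falls to 30 min or less only if W is at least 19.5 h. With only four valid days, one capped day adds 120/4 = 30 to 420/4 = 105 min/day. A participant who wears the device every night carries the full amount in the middle column.

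**Proportion scale, W = 16 h.** An average day is 460/960 = 47.9 %. After the cap it is (460 + 240)/1200 = 58.3 %, a shift of 10.4 points. The planned effect on this scale is 25/960 = 2.6 to 30/960 = 3.1 points. The distortion is 3.3 to 4.0 times the effect, compared with 240/30 = 8 to 240/25 = 9.6 times in minutes.

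**Trial level, W = 16 h.** The frequency of night wear is not given, so these figures are illustrations.

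- Bias: with night wear on every day, the arms would have to differ by 25/240 = 10.4 to 30/240 = 12.5 percentage points in the share affected to mimic the whole effect. With one capped day in seven, the figure is 25/34.3 = 73 to 30/34.3 = 87 points.
- Variance: if a share p of each arm carries an excess r, the SD becomes √(SD² + p(1 − p)r²). Take p = 5 % and SD 70. With r = 240 (every night), SD = √(4900 + 0.0475 × 57600) = 87.4. Power at 124 per group for 25 min then falls from 80 % to 61.5 %, and 192 per group would be needed. With r = 34.3 (one day in seven), SD = 70.4 and 125 per group are needed instead of 124.

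**The case against.** The strongest reply is that this is a fallback for non-compliance. Participants are told to take the device off at night, so capped days may be rare, and nothing in the document says how common they are. Both arms have the same device, instructions and wear weeks. The planned analysis compares changes, so a stable habit of night wear largely cancels within a participant. When night wear is occasional, the loss of power is trivial, as the last calculation shows. All of this stands, and it limits the claim about harm to the trial. It does not make the rule correct for the days to which it applies.

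The waking-hours wording in Outcomes does not rescue the rule. The same paragraph keeps up to 20 h as the recording time for a person presumed to have slept, and says exactly what is deducted.

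A reader might infer more than the document supports:

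- *That every affected participant's weekly value is inflated by more than the planned effect.* One capped day in seven adds only 17 min/day at an 18 h waking day and 26 min/day at 17 h.
- *That the proportion metric gives no protection.* It more than halves the relative distortion, though it does not remove it.
- *That recordings of 20 h or less which include sleep go uncorrected.* The article is silent on this, and a condensed article may leave such processing to the full protocol. Only the explicit cap is at issue.
- *That minutes depend too heavily on wear time, or that another metric should be primary.* Proportions are already planned alongside minutes, so this is a matter of preference.

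**Conclusion.** The point holds for the cap as written. It contradicts the waking-only definition and defeats its own purpose. On each capped day it leaves 120 to 420 min of sleep in the primary outcome for an assumed waking day of 18 to 13 h, against a planned group difference of 25 to 30 min/day. The direction and the per-day size are secure for any waking day shorter than 19.5 h, provided that sleep is registered as lying.

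The consequence for the trial's result is not established. A reader might infer that the comparison between arms is biased. That would require night wear to change differently between the arms, and the document gives no evidence that it does. Balanced night wear adds variance, by an amount that ranges from negligible to substantial depending on how many participants do it and how often. The rule deserves correction because it produces a wrong value by construction and is cheap to repair.

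**What to change.** Replace the 20 h cap in Outcomes. On days when the device was worn overnight, remove the night-time sleep period, identified from the posture signal within the night window or from bed and wake times if these are available. Apply the requirement of more than 10 h to the waking wear that remains. If sleep cannot be separated from waking time, treat the day as invalid. The four-day minimum then applies to the valid days.

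Do not delete the longest lying bout on days when the device was taken off at night. On those days it may be genuine waking rest, which is part of the outcome.

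The raw tri-axial data already being collected distinguish lying, sitting and standing. The posture accuracy quoted in the accelerometer section concerns standardised conditions and is not a validation of sleep detection, so the invalid-day option is needed as a fallback. The cost is one revised paragraph, some processing work and the loss of a few days. The change is best settled before outcomes are compared by arm.
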